# Immediate effects of hip strap and foot orthoses on self-reported measures and lower limb kinematics during functional tasks in individuals with patellofemoral osteoarthritis: protocol for a randomised crossover clinical trial

**DOI:** 10.1186/s13063-022-06676-0

**Published:** 2022-09-05

**Keywords:** Gait analysis, Walking, Patellofemoral joint, Hip, Function, Treatment, Rehabilitation, Foot orthoses, Biomechanics, Physiotherapy

## Abstract

**Background:**

Elevated patellofemoral joint stress has been associated with patellofemoral osteoarthritis (PFOA). Changes in lower limb kinematics, such as excessive femoral adduction and internal rotation and excessive rearfoot eversion during the stance phase of functional activities, may increase patellofemoral stress. There is a lack of studies that assess the effects of interventions for controlling femur and subtalar joint movements during functional activities on self-reported measures in individuals with PFOA. Thus, the primary aim of the study is to determine the immediate effects of the hip strap and foot orthoses during level-ground walking and the single-leg squat test on self-reported outcomes. The secondary aim is to investigate whether the hip strap and foot orthoses result in the kinematic changes that these devices are purported to cause.

**Methods:**

Twenty-nine individuals with PFOA aged 50 years or older will take part in the study. The main outcome is pain intensity. The secondary outcomes are other self-reported measures (global rating of change, acceptable state of symptoms, ease of performance, and confidence) and lower limb kinematics (peak femoral adduction and internal rotation, and peak rearfoot eversion). These outcomes will be assessed during functional tasks performed under three conditions: (i) control condition, (ii) hip strap intervention, and (iii) foot orthoses intervention. To investigate whether these interventions result in the lower limb kinematic changes that they are purported to cause, three-dimensional kinematics of the femur and rearfoot will be captured during each task. Linear mixed models with two fixed factors will be used to test associations between the interventions (control, hip strap, and foot orthoses) and conditions (level-ground walking and single-leg squat test) as well as interactions between the interventions and conditions.

**Discussion:**

To the best of the authors’ knowledge, this is the first study to evaluate the immediate effects of the hip strap and foot orthoses on self-reported measures and lower limb kinematics during functional tasks in individuals with PFOA. The findings of this study will enable future trials to investigate the effects of these interventions in rehabilitation programmes.

**Trial registration:**

ClinicalTrials.gov NCT04332900. Registered on 3 April 2020.

**Supplementary Information:**

The online version contains supplementary material available at 10.1186/s13063-022-06676-0.

## Background

Knee osteoarthritis is one of the leading causes of pain and functional disability throughout the world [1]. The most common and symptomatic compartment affected by knee osteoarthritis is the patellofemoral joint [2, 3]. In populations with knee pain or symptomatic knee osteoarthritis, the prevalence of patellofemoral osteoarthritis (PFOA) is 43% [4]. Thus, PFOA constitutes an important source of symptoms and has the potential to exert a negative impact on quality of life due to lifestyle restrictions resulting from pain and functional impairment [5]. The patellofemoral joint is often the first knee compartment affected by osteoarthritis and PFOA is associated with a 5.8-fold greater risk of damage in the tibiofemoral compartment [6]. Thus, PFOA should be considered the focus for the early treatment of knee osteoarthritis [7].

One of the classic symptoms of PFOA is pain in the anterior region of the knee, which is exacerbated by weight-bearing activities that place strain on the patellofemoral joint, such as kneeling and squatting [8]. An altered magnitude or distribution of loading in the patellofemoral joint has been associated with PFOA [8]. Changes in lower limb kinematics, such as excessive femoral adduction and internal rotation during weight-bearing activities, alter the contact between the patella and femoral trochlea, resulting in elevated patellofemoral joint stress [9]. Moreover, excessive subtalar joint pronation (assessed through rearfoot eversion) during the stance phase of gait may result in excessive femur internal rotation and, consequently, result in increased patellofemoral stress [10].

Two studies [11, 12] found also abnormal hip kinematics during functional activities in individuals with PFOA. Crossley et al. [11] found that such individuals walk with greater hip adduction during the late stance phase compared to healthy controls. Carvalho et al. [12] found that individuals with PFOA presented excessive hip adduction at 45° and 60° of knee flexion in both descending and ascending phases of the single-leg squat in comparison to healthy controls. To the best of the authors’ knowledge, only one study [13] investigated foot and ankle characteristics in individuals with PFOA, finding a decrease in ankle dorsiflexion and greater midfoot mobility through clinical measures. These changes may be associated with excessive rearfoot eversion during the stance phase of functional tasks in this population.

As changes in lower limb kinematics observed in individuals with PFOA may increase patellofemoral stress and result in an increase in clinical symptoms, interventions that control excessive femur and rearfoot movements could have an effect on symptoms. A hip strap consists of thin elastic material used to control movements of femoral adduction and internal rotation [14]. Previous studies have demonstrated that a hip strap significantly decreases pain intensity in individuals with patellofemoral pain (PFP) during running, the single-leg squat, and the step-landing task [15–17]. However, to the best of the authors’ knowledge, no studies have evaluated the effect of the hip strap on pain in individuals with PFOA. Foot orthoses with a medial wedge are used to control subtalar joint pronation and, consequently, decrease internal rotation of the femur [18]. Despite strong evidence of foot orthoses decreasing pain intensity in the short term in individuals with PFP [19–21], the effects on clinical symptoms in individuals with PFOA are conflicting [22–25]. To the best of the authors’ knowledge, this will be the first study to evaluate the immediate effects of the hip strap and foot orthoses on self-reported measures and lower limb kinematics during functional tasks in individuals with PFOA. The findings of this study are expected to assist future trials in investigating the effects of these interventions in rehabilitation programmes.

## Methods/design

### Aims

The primary aim of the proposed study is to determine the immediate effects of the hip strap and foot orthoses during level-ground walking and the single-leg squat test on self-reported outcomes. The secondary aim is to investigate whether both the hip strap and foot orthoses result in the kinematic changes that they are purported to cause.

The hypothesis is that the hip strap and foot orthoses will result in immediate improvements in pain intensity and other self-reported measures. We also hypothesise that the interventions will result in a decrease in peak femoral adduction and internal rotation as well as a decrease in peak rearfoot eversion.

### Study design and setting

A within-subject randomised crossover study will be conducted. This is the original version of the study protocol, which has been submitted to the *Clinical Trials* registry (clinicaltrials.gov) and was registered on 3 April 2020 under identification code NCT04332900.

The research will be conducted at the Evaluation and Intervention in Orthopaedics Laboratory (LAIOT) of the Physical Therapy Department of the Federal University of São Carlos (UFSCar) at a controlled temperature (21 to 23 °C).

The following methodology strictly follows the Standard Protocol Items: Recommendations for Interventional Trials 2013 checklist (SPIRIT) [26] and Template for Intervention Description and Replication (TIDieR) [27] to improve the information and quality of intervention reporting [28]. Additional File 1 presents the SPIRIT checklist. Consolidated Standards of Reporting Trials (CONSORT) [29] will be followed for reporting the results in a subsequent article.

### Ethical aspects

This study received approval from the Human Research Ethics Committee of the Federal University of São Carlos (UFSCar), SP, Brazil (certificate number: 24652419.0.0000.5504). The participants will receive clarifications regarding the procedures that will be performed throughout the study and will agree to participate by signing a statement of informed consent. The study will be conducted in accordance with the norms governing research involving human subjects stipulated in Resolution 466/12 of the National Health Board.

### Randomisation and masking

The participants will perform the tasks under three conditions (control condition, hip strap intervention, and foot orthoses intervention) in random order, which will be defined by a random number generator programme (www.randomization.com). Allocation concealment will be achieved using sequentially numbered opaque sealed envelopes. The order will be disclosed until the participants sign the statement of informed consent. A researcher not involved in the assessment or data collection processes will perform the randomisation step. This researcher also will be responsible for obtaining signed informed consent from the participants.

Due to the nature of the interventions administered in this study, the participants, the assessor who will administer the interventions, and the assessor who will conduct the data collection will not be blinded. Blinding will only be performed during the data processing and statistical analysis steps. The researcher conducting these steps will be blinded to the condition to which each participant was assigned. Thus, unblinding will not occur.

### Recruitment

Individuals from the city of São Carlos in the state of São Paulo, Brazil, will be invited to participate in the study. Advertisements for recruitment will be distributed at a university, printed in local newspapers, and posted on social networking websites. An assessor will perform a preliminary screening. An appointment will be scheduled with potentially eligible individuals who agree to participate to confirm eligibility.

### Sample

The R software was used to determine the sample size. Linear mixed model analysis was used to perform the calculation (package sjstats version 0.18.1), power = 80%; *α* = 0.05; large effect size of 1.25; number of clusters = six (three groups × two conditions). Using these parameters, the minimum sample size is 26 participants, to which 10% will be added to compensate for possible dropouts, leading to a sample of 29 participants.

The inclusion criterion is a clinical diagnosis of PFOA [30] adapted from the National Institute for Health and Care Excellence (NICE) guidelines [31]. The following criteria will also be required for inclusion: (i) age 50 years or over; (ii) anterior or retropatellar knee pain aggravated by at least two activities that place strain on the patellofemoral joint (e.g. squatting and stair ambulation); (iii) pain during these activities on most days in the previous month; (iv) pain severity during aggravating activities of ≥ 3 on an 11-point numerical rating scale; (v) symptoms present for at least three months; and (vi) no morning joint stiffness lasting longer than 30 min. The participants will need to have the ability to perform a single-leg squat to at least 60° of knee flexion and have a body mass index between 25 and 34.9 kg/m^2^.

The exclusion criteria are as follows: (i) recent treatment (e.g. knee injections within the previous 3 months); (ii) history of hip, knee, or foot surgery; (iii) physical inability to undergo the testing procedures; (iv) concomitant pain in other knee structures (including the tibiofemoral joint), hip, or lumbar spine; (v) history of knee or hip arthroplasty/osteotomy; (vi) neurological or systemic arthritis; (vii) use of a cane or other gait-assistance device; (viii) history of patellar fracture or recurrent subluxation; and (ix) score on the Mini Mental State Examination (MMSE) suggestive of dementia, taking into account the participant’s educational level.

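### The sample-size paragraph counts the six intervention-by-task cells as clusters, so its 80% power at effect size 1.25 does not describe this crossover

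*Protocol article*

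**What the plan says.** The Sample section describes the calculation as follows: "Linear mixed model analysis was used to perform the calculation (package sjstats version 0.18.1", with 80% power, alpha 0.05 and a "large effect size of 1.25; number of clusters" set to six, spelled out as "number of clusters = six (three groups × two conditions". It concludes that "the minimum sample size is 26 participants", "to which 10% will be added to compensate for possible dropouts, leading to a sample of 29 participants".

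Three other sections describe the design and analysis:

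- Study design and setting: "A within-subject randomised crossover study will be conducted".
- Procedures: every participant does both tasks under all three conditions in one session.
- Statistical analysis plan: intervention and task are the two fixed factors of a linear mixed model, subject is a random effect, and the significance level is 0.05 for all analyses.

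The primary outcome is pain intensity on a 0 to 100 mm VAS, averaged over five valid attempts per task.

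**The concern.** In a sample-size formula for clustered data, a cluster is a set of observations that are correlated with one another. In this trial those sets are the 26 to 29 participants, each with six cells. The six cells are crossed levels of two fixed factors, and there are no three groups of people. The Sample section therefore describes a different data structure from the one in the design and analysis sections.

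This matters because the power statement is what a reader uses to judge how sensitive the trial was for its primary outcome. As written, it presents a trial sized to detect a difference of 1.25 SD and credits it with 80% power there. The sensitivity of the crossover is different, and it depends on a within-person correlation that does not enter the stated calculation.

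**Working it through.** **Inputs from the protocol article.** Power 0.80, alpha 0.05, standardised effect 1.25, six clusters, 26 evaluable, 29 enrolled (Sample); crossover (Study design and setting); subject as random effect (Statistical analysis plan).

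**Assumptions not in the document.** Two-sided testing; the intra-cluster correlation (ICC) used in step 1; the within-person correlation r, shown as a range; equal r between all cells in step 4; the SD of the within-person difference in step 5.

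**1. Where 26 may come from.** A two-independent-sample t-test (noncentral t) with d = 1.25 needs 11.09 per group, a total of 22.19. Inflating this for k = 6 clusters:

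- cluster size m = 22.19 × (1 − ICC) / (6 − 22.19 × ICC)
- design effect = 1 + (m − 1) × ICC

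With ICC = 0.05, m = 22.19 × 0.95 / (6 − 1.109) = 4.31. The design effect is 1 + 3.31 × 0.05 = 1.1655, and the total is 22.19 × 1.1655 = 25.86, which rounds to 26.

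| ICC | Total |
|---|---|
| 0 | 22.2 |
| 0.01 | 22.8 |
| 0.05 | 25.9 |
| 0.10 | 31.7 |
| 0.20 | 68.2 |

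F-test versions with 1, 2 or 5 numerator degrees of freedom gave 8.7, 11.3 and 16.8. At ICC 0.05, taking k = 2 or 3 gave 47.3 and 33.4. So 26 is consistent with a two-group total inflated for six clusters, but the ICC had to be supplied to obtain it.

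**2. Dropout.** 26 × 1.1 = 28.6 and 26 / 0.9 = 28.9. Both round up to 29, so this step is right.

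**3. Power of the crossover at 1.25 SD, two interventions within one task.** Paired t-test (noncentral t), two-sided 0.05, with dz = 1.25 / √(2(1 − r)).

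| r | dz | Power, n = 26 | n for 80% |
|---|---|---|---|
| 0 | 0.884 | 99.1% | 13 |
| 0.3 | 1.056 | 99.93% | 10 |
| 0.5 | 1.250 | >99.99% | 8 |
| 0.7 | 1.614 | >99.99% | 6 |

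If 1.25 was meant as dz itself, the r = 0.5 row applies.

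**4. Intervention-by-task interaction contrast of 1.25 SD.** This is a difference of differences over four cells, with dz = 1.25 / √(4(1 − r)). At n = 26, power is 86.5% (r = 0, dz = 0.625), 95.5% (r = 0.3), 99.1% (r = 0.5) and 99.99% (r = 0.7).

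**5. What 26 completers can detect.** Solving the paired t-test for 80% power gives dz = 0.572 at n = 26 and 0.539 at n = 29. In raw-SD units at n = 26, d = 0.572 × √(2(1 − r)): 0.81, 0.68, 0.57 and 0.44 at r = 0, 0.3, 0.5 and 0.7. In millimetres, 0.572 × 15 = 8.6 mm if the SD of the within-person difference is 15 mm, and 0.572 × 20 = 11.4 mm if it is 20 mm.

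**6. Sensitivity at a smaller effect.** For a raw-SD difference of 0.4 at n = 26, power is 28% (r = 0), 50% (r = 0.5) and 87% (r = 0.8).

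**The case against.** The best defence is that nothing in the conduct of the trial depends on the error. At 1.25 SD the number is more than enough, the dropout step is correct, and randomisation and analysis are unaffected. The plan also commits to 95% confidence intervals and effect sizes, which will show what the data exclude whatever the power statement said. A condensed article may leave the correlation and the SD to a fuller document. All of this stands, and it limits the severity. It does not rescue the stated figures, because the cluster definition is printed and conflicts with the analysis section.

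Three stronger readings are tempting, and the document does not support them:

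- **That the authors used a two-independent-group formula.** A reader might infer this from the 25.86 in step 1. The article names a mixed-model calculation and states neither the formula nor an ICC. One free value fitted to one target is suggestive, not proof, and the point does not need it.
- **That the trial can detect effects less than half of 1.25.** This compares dz = 0.57 with a raw-SD 1.25. On one scale, the detectable d is 65% of 1.25 at r = 0 (0.81/1.25) and 54% at r = 0.3 (0.68/1.25). It falls below half only when r exceeds about 0.40.
- **That the detectable effect should be quoted at a multiplicity-adjusted alpha such as 0.0125.** The analysis plan fixes 0.05 throughout, so such a figure would have no basis unless a multiplicity rule were adopted.

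It is also fair that 99% is the power of a simple paired contrast, which the article does not name as primary. The interaction is harder to detect, yet even there power at r = 0 is 86.5%, not 80%.

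**Conclusion.** The point holds. The Sample section treats the fixed-factor cells as clusters, whereas the design and analysis make the participant the cluster, so 80% power at 1.25 is not a property of this trial. At 26 completers, power for 1.25 SD is at least 99.1% for a within-task comparison and at least 86.5% for the interaction contrast. 80% power for the within-task comparison is reached at dz = 0.57, that is d = 0.81 to 0.44 over r = 0 to 0.7.

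These figures assume two-sided 0.05, paired t-tests, a non-negative r and, for the interaction, equal correlation between cells. The error is conservative at the stated effect. The trial is not shown to be too small for 1.25, but nor is it shown to be adequate for a modest effect, where power depends heavily on r. Severity: should fix, as a correction to the power statement.

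**What to change.** Keep 29 participants. Delete the statement about six clusters and effect size 1.25, and replace it with wording such as: 26 completers give 80% power (two-sided 0.05, paired comparison) to detect a standardised within-person difference dz of 0.57 in VAS pain between a device and control within a task; in units of the between-person SD this is 0.81, 0.68, 0.57 or 0.44 if the within-person correlation is 0, 0.3, 0.5 or 0.7.

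Add the millimetre equivalent for an SD of the within-person difference that is labelled as an assumption, for example 8.6 mm for 15 mm or 11.4 mm for 20 mm. Quote a smaller-alpha figure only if a multiplicity rule is adopted.

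The cost is one rewritten paragraph, with no change to participants, procedures or analysis. The Trial status section says that recruitment has not started, so the correction can be made before any data exist.

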### Procedures

The participants will undergo a single session. At the beginning of the session, information will be collected on age, duration of symptoms, level of kinesiophoebia determined using the Tampa Scale of Kinesiophobia [32], usual and worst levels of pain experienced in the previous week using the visual analogue scale (VAS) [33], and symptoms related to the knee using the Anterior Knee Pain Scale (AKPS) [34] and Knee Injury and Osteoarthritis Outcome Score (KOOS-BR) [35]. Anthropometric and demographic data will also be collected for the characterisation of the study population. The MMSE [36] will be used to assess cognitive function and the ability to participate in the study. Cut-off points will be determined taking into account the educational level of each participant [36].

The participants will be assessed during level walking at a self-selected pace and the single-leg squat test under the three conditions, the order of which will be randomised: (i) control condition, (ii) hip strap intervention, and (iii) foot orthoses intervention. The control refers to the condition in which no interventions will be administered. The design of the study is shown in Fig. 1.

**Fig. 1 Fig1:**
[figure not shown]
Study design

The assessment will be performed on the affected lower limb in cases of unilateral PFOA or on the more painful knee in cases of bilateral PFOA [24]. If the participant reports equal pain intensity in both lower limbs, the lower limb to be tested will be chosen randomly using a simple raffle. For all evaluations, the participants will wear shorts, sports tops (in the case of women), and the same type of shoes (Nike® model *Flex Experience RN 2 MSL*), which will be provided to them by the assessors. The primary and secondary outcomes will be investigated during the performance of two functional tasks: level-ground walking and single-leg squat test.

Data collection and the therapeutic implementation steps will be performed by different assessors during the entire course of the study. Prior to data collection, the participants will have a period of familiarisation with both functional tasks and both therapeutic approaches that will be applied. The participants will perform the two functional tasks in a standardised order. The first will be level-ground walking at a self-selected pace and second will be the single-leg squat test, which is associated with a progressively larger patellofemoral joint load.

The presence of any pain or disability that may be related to the interventions and/or functional tasks will be considered as the criterion to discontinue the study.

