### Functional tasks

#### Level-ground walking

The participants will perform level walking at a self-selected pace on a 7.3-m walkway. The stance phase during level walking will be determined using an AMTI force plate (model OPT400600HF-2000) embedded in the centre of the walkway and synchronised with the three-dimensional motion analysis system with a sampling rate of 1200 Hz. The walkway will be covered with a rubberised fabric so that the participants will be unaware of the force plate and will consequently not alter their walking pattern. Each participant’s walking speed will be calculated by measuring the average horizontal velocity of the marker mounted on the posterior portion of the pelvis [37]. A trial will be considered valid if the foot of the evaluated lower limb comes into full contact with the force plate during the stance phase of gait [23]. If a trial is not considered valid, an additional trial will be performed. The data from the five trials of level-ground walking at a self-selected pace will be collected for analysis. A 1-min interval between trials will be respected.

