#### Single-leg squat test

To perform the single-leg squat test, the participants will stand on the lower limb being evaluated and be instructed to squat more than 60° of knee flexion (downward phase of the manoeuvre—2-s period) and return to the starting position (upward phase of the manoeuvre—2-s period) [12, 38]. A digital metronome will be used to control the single-leg squat rate (15 beats per minute). A repetition will be considered valid when the participant performs the single-leg squat with knee flexion of at least 60° within a period of 4 s without losing balance [12, 38]. If a repetition is not considered valid, an additional repetition will be performed. The data from five trials of the single-leg squat test will be collected for analysis. A 1-min interval between trials will be respected [39].

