### Primary and secondary outcome measures and assessment points

The primary outcome will be pain intensity. The secondary outcomes will be other self-reported measures and lower limb kinematic variables, as described below. The data will be collected at a specific time point (Fig. 2). All outcomes will be evaluated by the same assessor.

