#### Primary outcome

##### Pain intensity

Pain intensity will be measured using the visual analogue scale (VAS). This scale ranges from 0 to 100 mm, with the leftward extreme marked zero (absence of pain) and the rightward extreme marked 100 (worst pain imaginable). VAS scores will be computed by measuring the length of the line in millimetres from the extreme leftward mark (no pain) to the mark made by the participant. For the statistical purposes, the average score of the five valid attempts of each functional task will be used [33].

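### The discontinuation criterion covers any pain that may be related to the functional tasks, yet pain during those tasks is the primary outcome

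*Protocol article*

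**What the plan says.** **Stopping rule.** The Procedures section gives one criterion for stopping: "The presence of any pain or disability that may be related to the interventions and/or functional tasks". It attaches no severity, duration, site or comparison with usual pain.

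**Primary outcome.** Under the outcome measures heading: "The primary outcome will be pain intensity". Under Pain intensity, the analysed value is a VAS mean: "the average score of the five valid attempts of each functional task will be used".

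**Tasks.** Both tasks are repeated in every condition. For walking: "The data from the five trials of level-ground walking at a self-selected pace will be collected for analysis". For the squat: "The data from five trials of the single-leg squat test will be collected for analysis". Procedures adds that "The participants will perform the two functional tasks in a standardised order", with walking first and the squat second because the squat loads the joint more. Before any data are collected, participants are familiarised with both tasks and both devices.

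**Population.** The Sample section requires "anterior or retropatellar knee pain aggravated by at least two activities that place strain on the patellofemoral joint", and squatting is one of its examples. The pain must be rated 3 or higher on an 11-point scale and be present on most days of the preceding month.

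**Harms.** This section says that adverse events will be collected, reported and classed as serious or minor. It does not mention stopping, and it does not say that task pain is expected.

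**The concern.** The event that stops a participant and the event that the trial sets out to measure are described in the same terms: pain during walking or the single-leg squat. The study hypothesis is that the strap and the orthoses reduce this pain at once. Only a participant who has some task pain in the control condition can show such a reduction, and that participant meets the stopping criterion as worded.

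If staff follow the sentence, the participants who go through all three conditions are those with no task pain, who have no room to improve. If staff do not follow it, they depart from a written safety rule whenever they record a non-zero score and continue. The primary outcome cannot be collected as planned in a participant with task pain while the rule is kept.

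**Working it through.** No figure in the article depends on this sentence, so the check sets the texts side by side.

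1. **What triggers the rule.** Three features of the wording matter. It refers to any pain, so no severity threshold is implied. It requires only that the pain may be related, which is a low bar for causality. It names the functional tasks as well as the interventions, so it cannot be confined to harm from the devices.

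2. **What is measured.** The VAS runs from 0 (no pain) to 100 mm and is scored for the same two tasks. A score above 0 records that pain was present during the task. It is therefore both a planned data point and, literally, a trigger.

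3. **Whether another section narrows the rule.** Harms classifies adverse events but does not define task pain as expected. Sample sets entry criteria only. Data monitoring and the provisions for post-trial care do not address stopping. No section in the article exempts usual knee pain.

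4. **Who could meet it.** Everyone enrolled has pain on at least two patellofemoral-loading activities. Squatting is an example, not a requirement, and pain in level walking or in the single-leg squat is not itself an entry criterion. Some participants may therefore have no task pain. The article does not give the share who do.

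5. **When it could apply.** The criterion is not confined to scored trials. Familiarisation with both tasks precedes data collection, so a participant whose knee hurts on a practice squat would already meet it, before any score exists.

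6. **What is lost.** The design compares conditions within a person. A participant stopped in familiarisation contributes no scores. One stopped later contributes what was recorded up to then. The linear mixed model in the Statistical analysis plan section keeps such participants, but it cannot restore a within-person contrast for which one side was never observed. The loss falls on those with task pain, so it depends on the outcome itself.

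**The case against.** The strongest reply is that nobody would apply the sentence this way. Pain is paired with disability and tied to the interventions or tasks, which is the language of adverse events. The protocol recruits people in pain, tests the more painful knee in bilateral cases, and tells staff to average five pain scores per task. Staff with those instructions are unlikely to stop at the first non-zero mark. The article also condenses a fuller protocol, which may hold an operational threshold.

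Much of this stands. Harm caused by the study was very probably meant, and a missing threshold alone would be weak evidence. But the article does more than leave a threshold out. It states a rule, and the words chosen include the outcome. A rule that protects participants should be workable as written.

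The documents do not support four stronger readings that a reader might reach:

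- **That every participant would be stopped.** Pain in these two tasks is not required for entry.
- **That a calculable number would be lost, or that the sample would fall below its target.** The share with task pain is not given, and the order of tasks across conditions is in a figure not available here. Counting each stop against the 10% dropout allowance would also treat partly observed participants as total losses, although the planned model retains them.
- **That scores recorded before a stop would be discarded.** The analysis section plans to include individuals with missing data.
- **That unblinded assessors would stop people differently by condition.** This is possible, but it is speculation, and the lack of blinding affects any stopping rule in this trial.

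**Conclusion.** The criterion conflicts with the primary outcome as written and should be corrected. That conclusion rests on the text alone: the stopping sentence includes pain possibly related to the tasks, the primary outcome is pain in those tasks, and nothing in the article separates the two.

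The practical size is unknown. It depends on how many participants have task pain and on whether staff would apply the sentence literally, and the article settles neither. No expected loss of participants or of power can be derived. The direction under literal application is clear: the within-person contrast disappears in those in whom pain could fall.

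One assumption is made about meaning: discontinuing is taken to refer to the individual participant, which is the natural reading for a single-session study.

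**What to change.** Reword the one sentence in Procedures so that a participant is discontinued for:

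- new pain, intolerable pain, or pain markedly worse than usual, judged against a threshold fixed in advance (for example, a set VAS rise above the participant's usual level);
- injury; or
- inability to complete the task.

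Add that usual knee pain provoked by walking or squatting is not a trigger, and that the rule applies in familiarisation as well as in the scored trials. The investigators and the ethics committee should choose the threshold on clinical grounds. Procedures already collects usual and worst pain over the previous week on a VAS at the start of the session, so a reference level is available.

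The cost is a short amendment with ethics committee approval, as the section on protocol amendments requires. The article's Trial status section says that recruitment has not started, so the change can be in place before the first participant. It needs no additional data and no change to the sample size or the analysis model.
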